### Sample size estimate

The present study is a non-inferiority trial. The primary endpoint is the time period (days) required for PSL treatment (including PSL treatment for recurrence). PASS 11.0 software (NCSS, LLC, Kaysville, UT, USA.) was used to estimate sample size.

According to the previous literature [17, 18], the mean time was around 36 days with a standard deviation of 12 days. With a one-sided alpha level of 0.05, group sample sizes of 38 and 38 will achieve the power of 81% to detect non-inferiority with the margin of 7 days and the standard deviation of 12 days. Considering a drop-out rate of 20%, a sample size of 90 patients with a 1:1 allocation rate (45 patients per group) was finally determined.

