## Methods

### Study design

This is a multicenter, open-label, randomized, parallel non-inferiority trial. The study will be conducted at five academic hospitals in China: (1) Xiangyang Central Hospital, Affiliated Hospital of Hubei University of Arts and Science; (2) No. 1 Hospital of Yulin; (3) 3201 Hospital of Xi’an Jiao tong University Health Science Center; (4) Tangdu Hospital, Air Force Medical University; and (5) The Second Affiliated Hospital of Xi’an Jiaotong University.

Participants who fulfill the eligibility criteria will be randomly assigned with a 1:1 ratio to any of the following two groups: group 1 = low initial PSL dosage; and group 2 = standard initial PSL dosage. In group 1, 15 mg daily of PSL as the initial dosage for 14 days will be used, followed by a gradual taper by 5 mg every 7–14 days. In group 2, 30 mg daily of PSL as the initial dosage for 5–14 days will be used, followed by a gradual taper of 5–10 mg every 5–7 days (Figure 1).

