### Randomization methods and concealment mechanism

The stratified block randomization method will be used. Participants will be stratified by research center and the appropriate segment lengths will be selected. Based on the number of seeds, a random coding table of 92 participants will be generated using the statistical software SAS8.2 PROC PLAN. The randomized numbers will be segmented, retained, and managed by the third party who will not be involved in the data collection ([name]). The investigators in research centers will enroll the participants. When needed, the investigators will ask for numbers from the third party by telephone, using the order in which the participants will be treated, and the intervention scheme with that serial number will be provided.

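### The 20% drop-out allowance is miscalculated: 45 per arm leaves 36, not the 38 behind the 81% power, so power is about 79% if drop-outs yield no primary outcome

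*Protocol article*

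**What the plan says.** The section Sample size estimate declares the design ("The present study is a non-inferiority trial") and names days of prednisolone treatment as the primary endpoint. The planning values are a literature-based expectation ("the mean time was around 36 days with a standard deviation of 12 days"), the test level ("With a one-sided alpha level of 0.05"), and "the margin of 7 days and the standard deviation of 12 days". From these it concludes that "group sample sizes of 38 and 38 will achieve the power of 81" per cent. The next sentence moves from evaluable to randomised patients: "Considering a drop-out rate of 20%, a sample size of 90 patients with a 1:1 allocation rate (45 patients per group"). The Abstract gives the same total of 90.

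Two other places bear on the point. Statistical methods makes the full analysis set the basis for the primary outcome and adds a per-protocol analysis of all outcomes. Randomization methods and concealment mechanism describes centre-stratified blocks and says that "a random coding table of 92 participants will be generated".

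**The concern.** A drop-out rate is a fraction of the patients randomised. The number to randomise is therefore the evaluable number divided by one minus the rate. The article prints all three quantities (38 evaluable, 20% drop-out, 45 randomised per arm), and they do not fit together: removing 20% of 45 leaves fewer than 38.

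The power statement is the published justification for the size of the trial. If losses reach the planned rate and those patients contribute no primary outcome, the number analysed falls below the number on which the 81% rests, and power drops just under 80%.

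**Working it through.** **Inputs (Sample size estimate):** one-sided alpha 0.05; margin 7 days; SD 12 days; 38 evaluable per arm; stated power 81%; drop-out 20%; 45 randomised per arm. Allocation is 1:1 (Study design: "randomly assigned with a 1:1 ratio to any of the following two groups"). The true difference between arms is not stated. I take it as 0, which is supported by the fact that it returns the stated power.

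**Formula.** The normal approximation is power = Φ(7 / SE − 1.645), with SE = 12 × √(2/n). The t version uses the noncentral t distribution with 2n − 2 degrees of freedom and noncentrality 7/SE.

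**Step 1: reproduce the plan's figure (n = 38).** SE = 12 × √(2/38) = 2.753; 7/2.753 = 2.543; 2.543 − 1.645 = 0.898; Φ = 81.5%. By noncentral t, 80.9%. The stated 81% at 38 per arm is correct.

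**Step 2: the drop-out allowance.**
- Number needed to keep 38: 38/(1 − 0.20) = 47.5, so 48 per arm, 96 in total. On the total, 76/0.80 = 95, or 96 for equal arms.
- Number left from the plan's 45: 45 × 0.80 = 36.
- Drop-out at which 45 still leaves 38: 1 − 38/45 = 15.6% (7 patients per arm, where 20% is 9).
- Check on 48: 48 × 0.80 = 38.4, so 38 is preserved.

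Multiplying instead of dividing gives 38 × 1.20 = 45.6, close to the plan's 45. The article does not show how 45 was obtained, so this is only a possible explanation.

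**Step 3: power at the resulting numbers.**

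| Analysed per arm | Situation | Power, t | Power, normal |
|---|---|---|---|
| 38 | number stated in the plan | 80.9% | 81.5% |
| 36 | 45 randomised, 20% without a usable outcome | 79.0% | 79.7% |
| 45 | all randomised patients analysed | 86.5% | 86.9% |

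For n = 36 by the normal formula: SE = 12 × √(2/36) = 2.828; 7/2.828 = 2.475; 2.475 − 1.645 = 0.830; Φ = 79.7%.

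**Step 4: size of the gap.** The loss is 80.9 − 79.0 = 1.9 points (t) or 81.5 − 79.7 = 1.8 points (normal). The deficit is 38 − 36 = 2 evaluable patients per arm, or 96 − 90 = 6 randomised patients.

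**The case against.** **The 81% is attached to 38 per arm and is right there; the primary analysis may not lose the drop-outs.** Both parts are true. A reader might infer that the trial cannot deliver 81% power. The documents do not support that: the primary analysis uses the full analysis set, which the article does not define, so the number of drop-outs leaving that analysis cannot be read from it. With everyone analysed, power is about 86.5%. What stands is that the plan's own allowance supposes 20% loss, and under that supposition 36 remain. The per-protocol analysis could bear such a loss. The Treatment period section provides for study termination with a dose change, and patients handled that way may fall outside that set.

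**The loss is trivial.** It is about 2 points, and the SD of 12 days is itself a rounded literature value. The error does not touch the type I error, the margin or the interpretation of a non-inferiority conclusion. That limits the importance of the point, but the printed figures still disagree.

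**The 92-entry list.** A reader might infer that the document carries two conflicting sample sizes, 90 and 92, perhaps because 45.6 was rounded both down and up (2 × 46 = 92). The documents do not show this. The length of a randomisation list and an enrolment target are different quantities. With blocks stratified by centre, a list built from complete blocks can exceed the target; for illustration, 92 is 23 blocks of 4, although the block length is not stated. A list slightly longer than the target is not an error in itself, and no passage states the rounding derivation.

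**Conclusion.** The inflation step is wrong as written. The figures 38 evaluable, 20% drop-out and 45 randomised per arm cannot all hold: 45 per arm leaves 36, and keeping 38 would take 48. Conditional on 20% of patients giving no usable primary outcome, power is about 79% rather than 81%. This rests on a true difference of 0 and the plan's own SD, margin and alpha. It is a small error in the sample-size justification: the trial falls marginally below 80% under its own drop-out premise and is not seriously underpowered. The base calculation of 38 per arm is sound, and the difference between 90 and 92 is not part of the finding.

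**What to change.** Keep the target of 90 and correct the sentence in Sample size estimate, for example: *90 patients randomised (45 per group) with 20% drop-out leaves 36 per group and about 79% power; 81% power holds for drop-out up to 15.6%.* It would help to add that the loss applies to patients without a usable primary outcome, and that power is about 86.5% if all 45 per arm are analysed.

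The cost is a change of wording and a slightly less favourable power figure. No patients are added, and design, conduct and analysis stay as they are, which matters because the Trial status section says recruitment is under way. A short remark on why the randomisation list has 92 entries would be a courtesy to the reader, not a correction.

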### Data management

Investigators will collect and record data on the case report form and input the data to the electric database. All data will be stored in the database and inspected by a third party who is not involved in this study. The doctors and statisticians will not have access to these data until patient evaluations are completed.

The steering committee consists of the principal investigators, the local investigators at participating study sites, the statisticians, and the trial coordinators. The steering committee remains responsible for the interpretation of the data and drafts the final report that will be approved by all investigators.

The Data Monitoring Committee (DMC) will comprise representatives from the School of Public Health, Air Force Medical University of PLA. The DMC will be formed independently from the funders. The DMC will be responsible for the independent assessment of the validity and integrity of the randomized parallel control study. The DMC will meet twice a year or more if needed. A monitor will conduct monitoring visits once every 3 months and the auditing trial conduct will be independent from investigators and the sponsor.

## Discussion

Corticosteroids are important in the treatment of subacute thyroiditis; however, numerous adverse effects have been attributed to corticosteroids. Several retrospective reports have shown that long-term use of corticosteroids, even in low doses, is a significant independent predictor of adverse effects [12–16]. For example, a study found that the average daily prednisone dose was the strongest predictor of an adverse effect potentially attributable to glucocorticoid therapy (odds ratio = 4.5 for 5–10 mg and 32.3 for 10–15 mg) [12]. Studies also suggest that even short-term use of glucocorticoids may be associated with serious adverse effects. For example, a retrospective cohort study included 327,452 adults aged < 65 who received at least one short-term prescription over a 3-year period; results showed that there was an increase in the rates of sepsis, venous thromboembolism, and fracture [16]. Adverse effects may be not necessarily serious but displeasing to patients (e.g. Cushingoid appearance), life-threatening (e.g. serious infections), symptomatic (e.g. gastrointestinal ulcer), or largely asymptomatic until a later manifestation develops that requires medical attention (e.g. acute vertebral collapse). However, due to the relative short-term study period in the present trial, some long-term AEs cannot be collected and we may have difficulty in comparing adverse effects between groups, which is the limitation of the study. Meanwhile, because the risk is both dose- and duration-dependent, the time period of PSL usage was chosen as the primary endpoint; if non-inferior results are obtained, a lower initial dosage of PSL with a non-inferior time period will theoretically indicate reduced adverse effects.

This article presents the rationale and design of a RCT to test the effectiveness and safety of 15 mg daily of PSL versus 30 mg daily of PSL as the initial dosage in patients with SAT. This is the first RCT on this topic in Chinese people; by providing high-quality evidence, the present study will try to address the question of whether a lower initial dosage of PSL could provide non-inferiority effectiveness but with lower risk and more safety. If confirmed, our clinical practice may be modified to some extent, and patients may ultimately benefit.

### Trial status

The trial is currently recruiting participants. The recruitment began in June 2019 and is anticipated to end in March 2021. Trial registration number: ChiCTR1900023884. Registration date: 15 June 2019. The name of the registry is Chinese Clinical Trial Registry and the URL of the trial registry record is https://www.chictr.org.cn/.

## Data Availability

The datasets used and/or analyzed during the current study are available from the corresponding author on reasonable request.

## Abbreviations

SAT: Subacute thyroiditis
NSAIDs: Non-steroidal anti-inflammatory drugs
PSL: Prednisolone
ATA: American Thyroid Association
ESR: Erythrocyte sedimentation rate
CRP: C-reactive protein
VAS: Visual analog scales
